**BACKGROUND**

Diabetes Mellitus is a metabolic disorder of multiple aetiology characterized by, chronic hyperglycaemia with disturbance of carbohydrate, fat and protein metabolism resulting from defects in insulin secretion, insulin action, or both ^1.^  Diabetes Mellitus is broadly grouped into Type I (Insulin Dependent Diabetes Mellitus) and Type II (Non- Insulin Dependent Diabetes Mellitus); the latter is the focus of this study. Diabetes Mellitus in pregnancy consists of pre-gestational Diabetes Mellitus and Gestational Diabetes Mellitus. Gestational Diabetes Mellitus is characterized by hyperglycaemia of varying severity, diagnosed during pregnancy (without previously known diabetes) and usually (but not always) resolving within six weeks of delivery^1^. The prevalence of diabetes mellitus world- wide is projected to increase.^2^

A study in Nigeria estimated the incidence of Diabetes Mellitus (DM) among pregnant women as 1.7%. Pre-gestational diabetes accounted for 39% while Gestational Diabetes was responsible for 61% of cases.^3^ There is no national data on the prevalence of DM among pregnant women in Ghana. Data from Greater Accra estimates the crude prevalence of Diabetes Mellitus as 6.3%^4^. It is estimated that 3-10 % of pregnancies are complicated by Diabetes Mellitus.^5, 6^

Diabetes mellitus is an important complication of pregnancy with adverse effects on both maternal and fetal outcomes. Treatment options of diabetes complicating pregnancy are limited. Several classes of medicines have been developed based on the pathophysiology of diabetes and are being used as monotherapy or combination therapies with varying efficacies in the general population of diabetics. In pregnant diabetics however, exercise and dietary management followed by insulin therapy where dietary management have failed is the general trend. Few countries have added some oral hypoglycaemic agents to this management, but lack of adequate data on efficacy and safety in the pregnant population has slowed this development in several countries.

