**AIM**

The aim of this study is to determine if metformin monotherapy or metformin in combination with insulin is more effective at attaining and maintaining glycaemic targets compared to insulin monotherapy in the management of gestational diabetes mellitus and type 2 pre-gestational diabetes mellitus in Ghanaians.

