**METHODOLOGY**

STUDY DESIGN

The study design is a prospective, randomized comparative study. Participants will be randomly assigned into one of the two treatment groups. For a set of four (4) patients seen at the clinic for the first time, they will be made to ballot by picking randomly one paper with an inscription each from an opaque envelope. This assigned participants to one of the two treatment groups – insulin and metformin. This will be repeated till the sample size is attained. The sequence of picking will be in the order in which they reported to the clinic; “first to report, first to pick”**.**  The participants in each group will be matched for age, parity, gestational age, pre-treatment weight and pre-treatment glycaemic profile.

Treatment will be administered to each according to the study treatment protocols. Subjects in both groups will follow the routine antenatal schedule and their blood glucose levels will also be checked and recorded during these visits according to existing protocols. For in-patients a similar routine will be followed.

STUDY AREA

The study will be conducted at the Maternity Unit and the Diabetes Centre of Korle Bu Teaching Hospital. It will involve both in- patients and out-patients in these units.

STUDY SUBJECTS

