**Eligibility criteria**

Eligible subjects will be women aged 18 to 45 years who are pregnant with single fetus at gestational age of 20 to 30 weeks and have been diagnosed with type 2 DM or Gestational Diabetes and met the Hospital’s criteria for starting insulin therapy. The criteria for the diagnosis of GDM and DM will be a plasma glucose concentration of greater than or equal to 7 mmol/L after an overnight fast or plasma glucose concentration of equal to or greater than 11.1 mmol/L 2 hours after a 75g glucose drink.^1^

The current criteria for starting insulin therapy in patient with GDM at the diabetes clinic of KBTH are at least one following:

- FBS > 5.1 mmol/l
- 1HPG > 10.0 mmol/L or
- 2HPG > 8.5 mmol/L.

Subjects diagnosed according to the above criteria that are unable to achieve the above targets following management on diet and exercise will be eligible for the study.

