**Exclusion criteria**

Exclusion criteria will include patients with insulin dependent Diabetes Mellitus and patients with contraindications to metformin therapy.

SAMPLE SIZE DETERMINATION

Power calculation: The power calculation is based on the difference in 2HPG expected between the metformin and insulin groups at 34 weeks gestation. Using the two sampled mean formula^34^, the estimated sample size was 47 per group. From pre-trial estimates the minimum difference in mean 2HPG levels between the two groups of 4mg/dl (0. 22 mmol/l) is required to give a power of 80% to the study at a significance level of α = 0.05.We recruited 52 in each group to allow for a 10% non-respondent rate

TREATMENT PROTOCOL

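### Diabetes type is left out of the ballot and of the stated 2HPG test, although the trial enrols two types; the cost is precision and interpretability, not bias

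*Protocol*

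**What the plan says.** The AIM names one combined population: treatment is compared "in the management of gestational diabetes mellitus and type 2 pre-gestational diabetes mellitus in Ghanaians". Eligibility criteria admit women who "have been diagnosed with type 2 DM or Gestational Diabetes and met the Hospital’s criteria for starting insulin therapy". The clinic's thresholds for starting insulin are then introduced for GDM only: "The current criteria for starting insulin therapy in patient with GDM at the diabetes clinic of KBTH are at least one following".

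Allocation is described under METHODOLOGY, Study design. "For a set of four (4) patients seen at the clinic for the first time, they will be made to ballot", and "The sequence of picking will be in the order in which they reported to the clinic". No separate ballot by diabetes type is mentioned. The same paragraph states: "The participants in each group will be matched for age, parity, gestational age, pre-treatment weight and pre-treatment glycaemic profile". Diabetes type is not on that list, and the ballot contains no step that would produce the matching.

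STATISTICAL ANALYSIS gives a one-tailed t-test for means and a two-way repeated-measures ANOVA for trends. Neither mentions diabetes type. The only figure on the mix of types is in BACKGROUND, from a Nigerian study: "Pre-gestational diabetes accounted for 39% while Gestational Diabetes was responsible for 61% of cases".

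**The concern.** BACKGROUND itself separates the two conditions: GDM is first found in pregnancy and usually resolves after delivery, whereas pre-gestational diabetes is already present. Diabetes type is therefore a plausible predictor of 2HPG, of the need for supplemental insulin and of birth weight. With about 50 women per arm, a ballot that ignores type will often leave the arms with visibly different mixes.

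Two things are at stake. If type predicts 2HPG, its variance stays in the error term of the unadjusted test and power is lost. And if the arms end up with different mixes, a reader of the results cannot easily tell how much of an observed difference reflects the mix. The protocol names five balance factors and omits the one that defines its two populations.

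**Working it through.** **Inputs.** From SAMPLE SIZE DETERMINATION: 47 evaluable and 52 recruited per group, difference 0.22 mmol/L, power 80%, α = 0.05. From BACKGROUND: 39% pre-gestational, used here as an assumption for the trial's mix, with 20% to 50% as a range. Not in the protocol: the SD of 2HPG, and the gap D in mean 2HPG between the two types.

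**Step 1: the SD behind the plan's own figure.** The figure of 47 cannot be reproduced forwards because no SD is stated. Solving backwards, SD = 0.22 × √(47/2) / (z_α + z_β):
- two-sided: 0.22 × 4.848 / (1.960 + 0.842) = 0.381 mmol/L
- one-sided: 0.22 × 4.848 / (1.645 + 0.842) = 0.429 mmol/L

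Both are shown because the power text does not state sidedness, while the analysis section uses a one-tailed test.

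**Step 2: how uneven the arms can be.** With 104 women, 39% is about 41 with type 2 diabetes. If type is unrelated to arrival order, the number falling in one arm of 52 is hypergeometric, whether or not each set of four is split evenly.
- SD of the difference in type 2 share: 0.096, or 9.6 points. The approximation √(2 × 0.39 × 0.61 / 52) gives the same 0.096.
- Chance of a difference of 7/52 (13.5 points) or more: 0.23.
- For a type 2 share of 20% to 50%, the SD is about 8 to 10 points.

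**Step 3: what an imbalance does to mean 2HPG.** Shift = difference in share × D. Even if type explained all the variation in 2HPG, D could not exceed SD / √(0.39 × 0.61) = SD / 0.488 without contradicting the SD from Step 1.

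| | Two-sided SD 0.381 | One-sided SD 0.429 |
|---|---|---|
| Largest D (mmol/L) | 0.78 | 0.88 |
| 1-SD shift, 0.0957 × D (mmol/L) | 0.075 | 0.084 |
| As a share of 0.22 | 34% | 38% |
| 1.96-SD shift (mmol/L) | 0.15 | 0.16 |

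The ceiling on the 1-SD shift equals SD × √(2/52), so it does not depend on the assumed mix. At these limits, the chance that imbalance alone produces a shift of 0.22 is 0.3% to 0.9% by the normal approximation and 0.5% to 1.6% by exact count.

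**Step 4: what a larger shift would need.** A shift of 0.22 needs D = 0.22 / 0.0957 = 2.3 mmol/L at a 1-SD imbalance, or D = 0.22 / (1.96 × 0.0957) = 1.2 mmol/L at a 1.96-SD imbalance. Those gaps alone create an overall SD of 2.3 × 0.488 = 1.1 or 1.2 × 0.488 = 0.57 mmol/L, above the SD on which 47 per group rests.

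**Step 5: the precision at stake.** The share of variance due to type is D² × 0.39 × 0.61 / SD². For an assumed D of 0.25 mmol/L this is 0.0149 / 0.145 = 10% (two-sided SD) or 0.0149 / 0.184 = 8% (one-sided SD). For an assumed D of 0.5 it is 0.0595 / 0.145 = 41% or 0.0595 / 0.184 = 32%. Adjusting for type would remove that share from the error variance.

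**Step 6: results by type.** With about 20 type 2 women per arm, the 95% half-width for the arm difference is 1.96 × SD × √(2/20) = 0.24 to 0.27 mmol/L, wider than the 0.22 sought.

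**The case against.** Several counter-arguments have force.

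- **Chance imbalance is not bias.** Under random allocation the between-type variance is already in the standard error of the t-test, so the type I error is preserved. Leaving a prognostic factor out of the randomisation is a common and valid choice. This stands, and it fixes the nature of the point.
- **A reader might infer that imbalance in type could rival the 0.22 mmol/L effect.** The protocol does not support this. It gives no between-type gap, and Steps 3 and 4 show that such shifts need a gap that conflicts with the SD implied by 47 per group. If the gap really were that large, the sample size would be the more serious problem.
- **Matching on pre-treatment glycaemic profile would remove part of any type effect.** It would if achieved, but the ballot provides no means of achieving it.
- **Adjustment and subgroup tables may be in an analysis plan that is not at hand.** Their absence is therefore not held against the protocol. Stratified allocation, however, is a protocol matter that no later analysis plan can restore.
- **A reader might infer that the type 2 part of the aim goes unanswered.** The hypotheses and objectives are pooled, referring to pregnant diabetics and pregnant women without distinction, and a pooled estimate answers a pooled question. What it does not support is a separate conclusion for type 2 women.
- **The 39% is weak evidence for this trial's mix.** It comes from a Nigerian series, not from women at 20 to 30 weeks who failed diet and exercise. The range of 20% to 50% changes the imbalance SD little, and the ceiling in Step 3 not at all.

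**Conclusion.** The point holds as an inexpensive improvement to the design. The protocol enrols two types of diabetes and neither stratifies the ballot nor matches on type, and its stated t-test is unadjusted for type. A between-arm difference of about 10 points in type 2 share would be an ordinary event. Its effect on mean 2HPG is at most about 0.08 mmol/L at 1 SD, roughly a third of the target difference, if the SD implied by the protocol's own sample size is right. The actual shift depends on a between-type gap that the protocol does not state, and it may be much smaller. The consequence is lost precision and a result that is harder to interpret; neither systematic bias nor an inflated type I error follows.

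**What to change.** In METHODOLOGY, Study design, keep two ballots, one for women with GDM and one for women with pre-gestational type 2 diabetes, with two papers for each treatment in every set of four. In STATISTICAL ANALYSIS, include diabetes type as a factor in the 2HPG comparison so that the analysis matches the allocation. If results are shown by type, present them descriptively with confidence intervals, and draw no separate conclusion for type 2 women from the pooled mean.

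The cost is a second envelope, one more model term and possibly one incomplete set of four per type. The sample-size section is partly in the past tense. If allocation has already taken place, only the analysis change remains available, together with a table of diabetes type by arm.

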**SPECIFIC OBJECTIVES**

- To determine and compare blood glucose profile in pregnant women treated with metformin versus insulin.
- To determine the additional insulin requirements and the blood glucose profile in subjects who may require supplemental insulin in the metformin group.
- To measure and compare maternal weight gain in the index pregnancy between mothers treated with metformin versus insulin.
- To measure and compare birth weight between babies in the metformin and insulin groups.

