**ABSTRACT**

**Background:** Diabetes mellitus is an important complication of pregnancy with adverse effects on both mother and fetus. Poor control of pre-gestational diabetes during the period of organogenesis increases the risk of major congenital malformations. While insulin is effective in controlling high blood glucose levels, otherwise resistant to diet and exercise management, several factors hinder its use. Metformin has been found to be a convenient, cheap, effective and safe hypoglycaemic agent in some countries and it is likely to do same among Ghanaian women.

**Aim:** The main aim of this study is to determine if metformin monotherapy or metformin in combination with insulin is equally effective at attaining and maintaining glycaemic targets compared to insulin monotherapy in the management of gestational diabetes mellitus and type 2 pre-gestational diabetes mellitus in Ghanaians.

**Methodology:**  A prospective randomized comparative study is proposed. Patient selection and randomization will be done using balloting with opaque envelopes. Participants will be followed through their index pregnancy with 2-weekly glycaemic profile monitoring and maternal weight gain. Babies delivered will be followed till the sixth week post-delivery measuring birth weight, incidence of birth trauma and neonatal intensive care unit (NICU) admission rates. Both laboratory and clinical data will be recorded and analyzed.

**Expected outcome:** It is expected that pregnant diabetics treated with metformin will have a lower 2HPG levels at the end of the study than those treated with insulin. The 2-hour post prandial glucose (2HPG) level is the measure selected to estimate the effectiveness of glycaemic control.

In addition NICU admissions are expected to be higher in the insulin group than metformin group.

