**HYPOTHESES**

- The glycaemic control will be equally effective with metformin therapy compared to insulin in pregnant diabetics in Ghana.
- Weight gain in mother and baby will be significantly lower on metformin therapy compared to insulin.

*Rationale:* Metformin has been shown to be equally effective and safe as insulin in the management of GDM. Poor compliance to insulin due to high cost, accessibility, storage difficulties and the discomfort of repeated injections is expected to make metformin a more suitable choice.

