**Treatment failures**

Supplemental insulin for treatment failures in the Metformin group will be prescribed according to the same protocols in the insulin group.

DATA COLLECTION

Basic demographic data will be recorded. They will be followed through their index pregnancy, with 2-weekly blood glucose checks in hospital. All laboratory samples will be collected and analyzed at the diabetes research laboratory by staff of the same laboratory. Venous blood will be used for blood glucose profile analysis. Analysis of Fasting Blood Glucose (FBG), one- hour post-prandial glucose (1HPG), two- hour post-prandial glucose (2HPG) will be done using the Mindray BS-400^®^ (Mindray Medical Int. Ltd, China) chemistry analyzer. The method for glucose determination will be enzymatic photometric testing. Urinalysis, weight records (using Seca^®^(gmbh&Co. Kg Germany)) and cost of treatment will also be documented. The optimal dose of metformin required for optimal glycaemic control will be recorded for each patient. Peri-partum events like gestational age at delivery, type of delivery, fetal birth weight, and NICU admissions will be retrieved from patient notes.

STATISTICAL ANALYSIS

In analyzing the data, summary statistics will include appropriate tables and charts. Categorical data will be represented by pie and bar graphs and continuous data with histograms.

For inferential statistics, significant difference of mean observations using one-tail student’s t-test and z-score for differences in proportions where applicable. The differences in trends of glycaemic profile over time between the study groups will be assessed by two-way repeated measures analysis of variance (ANOVA).

Significance level (p-value) will be set at α = 0.05. Data analysis will be done using statistical package for social science **(SPSS** version 20).

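### Maternal weight gain is not tied to the treatment period, and the unadjusted t-test ignores a roughly two-fold range in time on treatment

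*Protocol*

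**What the plan says.** The Hypotheses section of the Protocol predicts: "Weight gain in mother and baby will be significantly lower on metformin therapy compared to insulin". The matching item under Specific Objectives is "To measure and compare maternal weight gain in the index pregnancy between mothers treated with metformin versus insulin". The Expected Outcome section lists maternal weight gain among the secondary outcomes.

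The Eligibility criteria admit women "pregnant with single fetus at gestational age of 20 to 30 weeks". The Abstract describes follow-up as "Participants will be followed through their index pregnancy with 2-weekly glycaemic profile monitoring and maternal weight gain". Data Collection adds that weights are recorded. The only baseline weight mentioned is in Study Design, which says the groups will be "matched for age, parity, gestational age, pre-treatment weight and pre-treatment glycaemic profile".

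For means, Statistical Analysis gives "significant difference of mean observations using one-tail" Student's t-test, where applicable. Repeated-measures ANOVA is reserved for trends in the glycaemic profile. No covariate adjustment is stated for any outcome, and no start or end weight is given for the gain.

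**The concern.** The hypothesis concerns gain while on therapy, but the objective identifies only the pregnancy in which gain is measured. If gain is counted from the pre-treatment weight, as the other sections suggest, a woman who enters at 20 weeks has about twice as long to gain weight as one who enters at 30 weeks. An unadjusted comparison of means leaves that difference in the error term, although it is known at entry and can be removed.

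At stake is the precision of the test of half of the second hypothesis, in a trial with about 50 women per arm. A real difference in weight gain becomes somewhat harder to see, and a chance difference in entry age between the arms passes straight into the estimate.

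**Working it through.** **The plan's own figure.** There is none for weight gain. The sample size of 47 per group, raised to 52, is for the 2-hour post-prandial glucose and has no bearing here.

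**Inputs**
- Entry window: 20 to 30 weeks (Eligibility criteria).
- Women per arm: 52 recruited, 47 before the allowance for non-response (Sample Size Determination).
- Assumed: term at 40 weeks, entry spread evenly over the window, and a steady gain of 0.3 to 0.5 kg per week. The Protocol gives none of these three.

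**1. Time on treatment.** Shortest: 40 − 30 = 10 weeks. Longest: 40 − 20 = 20 weeks. The ratio is 2.

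**2. Spread of that time.** The SD of a uniform variable is its range divided by √12: 10/√12 = 2.89 weeks.

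**3. Variation in gain caused by entry time alone**
- At 0.3 kg per week: 2.89 × 0.3 = 0.87 kg.
- At 0.5 kg per week: 2.89 × 0.5 = 1.44 kg.

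The SD is therefore about 0.9 to 1.4 kg. Women at the two ends of the window differ by 10 weeks, or 3 to 5 kg of expected gain, before any treatment effect.

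**4. Chance imbalance between arms.** The standard error of the difference in mean entry age is SD × √(2/n).
- n = 52: 2.89 × √(2/52) = 0.57 weeks, which is 0.17 to 0.28 kg.
- n = 47: 2.89 × √(2/47) = 0.60 weeks, which is 0.18 to 0.30 kg.

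**5. Bias or precision?** Under randomisation, entry age has the same expected distribution in both arms, so the expected difference in mean gain is unchanged. Only its variance rises.

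**6. What cannot be computed.** The share of variance that adjustment would remove is s²/SD², where s is the 0.9 to 1.4 kg above and SD is the total SD of weight gain. The Protocol gives no SD for weight gain and no target difference, so a loss of power cannot be derived from it.

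**7. Does the stated matching deal with this?** Study Design says the groups will be matched on gestational age and pre-treatment weight. The allocation it describes is a ballot within sets of four women, in order of arrival, with no stratification. Nothing in that procedure produces the matching. Even if balance were achieved, an unadjusted t-test would still count the spread in entry time as error, so its standard error would be larger than necessary.

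**The case against.** **Matters of detail for a SAP.** The derivation of a secondary outcome and its covariates are often left to the SAP, which is not available here. The t-test sentence is general, qualified by applicability, and not assigned to weight gain by name. An unadjusted t-test is valid in a randomised trial, and its standard error already covers chance imbalance in entry age. All of this is fair. It limits the point to efficiency and clarity, and the bare absence of a detailed definition would not be a finding. What remains is that the Protocol does state a method for comparing means, states no adjusted alternative, and names the two baseline variables that would make the comparison sharper.

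**A stronger reading that the Protocol does not support.** A reader might infer that gain is measured over the whole pregnancy. On a 40-week term, 20/40 to 30/40, or 50% to 75%, would then precede treatment and, on this view, dilute the effect. The objective's phrase identifies which pregnancy is meant; it sets no start weight. The Abstract attaches weight gain to follow-up after enrolment, and Data Collection uses the same expression for prospective follow-up: "They will be followed through their index pregnancy, with 2-weekly blood glucose checks in hospital". The hypothesis speaks of gain on therapy, the only baseline weight named is the pre-treatment one, and no pre-pregnancy or booking weight appears anywhere. Even on the whole-pregnancy reading, gain before randomisation would be balanced in expectation. It would add variance but would not shrink the expected difference in kilograms. Any power figure built on that reading would rest on assumed SDs.

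**Conclusion.** The point holds as a modest one about precision and definition. The Protocol does not tie maternal weight gain to the treatment period, and its only stated test for means ignores a roughly two-fold range in time on treatment. The avoidable variation has an SD of about 0.9 to 1.4 kg. Chance imbalance in entry age moves the between-arm difference by a standard error of about 0.2 to 0.3 kg.

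These sizes rest on a 40-week term, uniform entry and 0.3 to 0.5 kg per week. A narrower actual spread of entry ages or a slower gain would reduce them. No bias is shown, no loss of power can be quantified from the Protocol, and the outcome is secondary. The change is worth making because it costs almost nothing, not because the comparison as written is invalid.

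**What to change.** Two sentences would do it.

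- **Specific Objectives:** state that maternal weight gain is the last antenatal weight before delivery minus the pre-treatment weight at randomisation.
- **Statistical Analysis:** state that the arms are compared on this gain by ANCOVA, with gestational age at entry and pre-treatment weight as covariates, in place of the unadjusted t-test.

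Use gestational age at entry rather than time from entry to delivery. Entry age is fixed before allocation, whereas the timing of delivery comes after it and could itself be affected by treatment.

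No new data are needed. Gestational age at entry is required for eligibility, Study Design names pre-treatment weight, and Data Collection provides for weight records. ANCOVA is available in the software already named. It uses two degrees of freedom, which is negligible with about 50 women per arm. The result is an adjusted difference in treatment-period gain; unadjusted means can be shown beside it.
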